### Blinding

This study is not a global double-blind study in Stages 1 and 2, as we have 3 drugs with different physical characteristics, rendering global blinding impossible. Both the participant and investigator can know, after randomization, to which drug group the patient was allocated. However, none will know whether the capsule or coated tablet to be administered contained the active drug or PbO, ensuring blinding of participants and investigators within that specific group, as well as the outcome assessors.

In Phase 3, the global blinding of the stage is possible, since we will have only one active group and a PbO.

A partnership will be established with a handling pharmacy duly licensed to carry out the fractioning, repacking, labeling and blinding process of the drugs. The pharmacy will deliver all the drugs to a logistic contractor, who will deliver them to the centers.

### Data collection, management and analysis

#### Collection and management methods

The data collection system to be adopted in the development of this study is widely used in research projects and easily accessible via the web with Redcap^®^ software. Only users qualified by the system administrator receive access, each registered user accesses the system only with their login and password, and the sharing of this information between project collaborators is prohibited.

The data collected and the participant timeline are described in table 5.

**Table 5 t5:** Participant timeline and data collection

				Onset: April 2021							End: March 2022				
**Screening**	-t1	T1	D1	D2	D3	D4	D5	D6	D7	D8	D9	D10	D14	D15	D28
Screening	x														
Clinical history	x														
Eligibility	x														
ICF	x														
Screening tests	x														
ECG	x				x										
Allocation		x													
**Interventions**	**-t1**	**T1**	**D1**	**D2**	**D3**	**D4**	**D5**	**D6**	**D7**	**D8**	**D9**	**D10**	**D14**	**D15**	**D28**
Intervention drug/drugs			x	x	x	x	x	x	x	x	x	x			
Placebo			x	x	x	x	x	x	x	x	x	x			
**Data and tests collection**	**-t1**	**T1**	**D1**	**D2**	**D3**	**D4**	**D5**	**D6**	**D7**	**D8**	**D9**	**D10**	**D14**	**D15**	**D28**
Demographic data	x														
RT-PCR	x														
Safety checks	x				x			x				x			
Baseline data			x												
Concomitant therapies			x	x	x	x	x	x	x	x	x	x			
Daily data			x	x	x	x	x	x	x	x	x	x	x	x	x
Primary outcome		x			x			x				x		x	
Secondary outcomes			x	x	x	x	x	x	x	x	x	x	x	x	x

D - day; ICF - Informed Consent Form; ECG - electrocardiogram; RT-PCR - real-time polymerase chain reaction.

#### Retention

Data will be collected from patients admitted to the ICU/hospital, which reduces the risk of data loss due to loss of follow-up. Telephone contact will be made centrally by professionals who have not participated in other stages of the study.

- **Postdischarge follow-up:** Patients discharged less than 15 days after randomization will be contacted by telephone daily until D10 and on D15 and 28 and questioned using a structured form by an interviewer who is blinded to the research participant’s allocation group. In this contact, the participant or his or her family member will be asked about the observation of adverse events, and ordinal scales of 6 and 7 points will be applied for the secondary outcomes.

### Statistical methods

The main analysis of the data from this study will be performed on patients of the intention-to-treat (ITT) population. The definition of the analysis populations and more details on statistical methods are available in the Statistical Analysis Plan. The analyses will be performed with R software (R Core Team, 2020).

All the different PbOs for ATV, DCV and SOF will always be analyzed together as a single PbO group.

### Analysis of primary outcomes

#### Phase II/1

In Phase II/1, patients will be allocated in ratio of 3:3:3:1:1:1 (3 for each treatment group and 1 for PbO). For Phase II/1, the parameter of interest for the decision will be the comparison of the decay rates of the viral load logarithm from real time polymerase chain reaction (RTPCR) to COVID-19 in 9 days between the treatment groups compared with the control using a mixed linear model.

The interim analysis, which is planned to begin when 126 patients are randomized and followed for at least 10 days, will be exclusively conducted for a patient safety assessment (based on safety outcomes and adverse events).

At the end of Phase II/1, each group will be compared with the PbO group considering a significance level for each comparison of 0.067 (Bonferroni correction for multiple comparisons), such that the global type I error of Phase II/1 will be 0.20. If no treatment is significantly different from the PbO group at the stipulated level of significance, the study will be terminated at this stage.

Among the treatments significantly different from the PbO group in relation to the linear rate of viral load decay, the one with the highest rate of decay and considered safe by the independent study safety committee will be a candidate treatment for inclusion in Phase II/2 of the study. It will be combined with the drug responsible for the second highest linear decay rate to comprise the second Phase II/2 treatment group.

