### Sample size

We intend to include 252 patients in Phase II/Stage 1 (189 in the active groups and 63 in the PbO group) and 189 patients in Phase II/Stage 2 (126 in the active groups and 63 in the PbO group). For Phase III, 564 additional participants will be randomized (376 in the active group and 188 in the PbO group). Thus, at the end of Phase III, 314 patients will have been evaluated in the PbO group and between 439 and 502 patients will have been evaluated in the treatment group if the study persists through the three phases. More details about the sample size calculation are described in Supplementary material 2 (Statistical Analysis Plan).

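### Phase II/1 reports the Bonferroni upper bound of 0.20 as the attained global error; with a shared placebo it is about 0.16, and a Dunnett test would use the declared level more fully

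*Protocol article*

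**What the plan says.** Under Analysis of primary outcomes, Phase II/1, the article sets the decision rule: "each group will be compared with the PbO group considering a significance level for each comparison of 0.067 (Bonferroni correction for multiple comparisons"), and concludes that this is done "such that the global type I error of Phase II/1 will be 0.20". The estimate is the difference in slope of log viral load "between the treatment groups compared with the control using a mixed linear model". The stage's single interim analysis is for safety only, so it spends no efficacy error.

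The comparator is one group. Statistical methods says: "All the different PbOs for ATV, DCV and SOF will always be analyzed together as a single PbO group". Sample size gives the numbers: "We intend to include 252 patients in Phase II/Stage 1 (189 in the active groups and 63 in the PbO group").

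The rule can end the trial. The sentence opening "If no treatment is significantly different from the PbO group at the stipulated level of significance" goes on to stop the study at this stage.

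The article does not say whether the tests are one-sided or two-sided, and it gives no power for this stage. It refers the sample size details to the statistical analysis plan.

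**The concern.** Bonferroni adds the three error rates as if false positives in different arms never coincided. Here they often would: if the pooled placebo group has a slow decay by chance, all three drugs look good together. The chance of at least one false positive is therefore below the sum of the three levels, and the article gives the sum as the rate the stage will have.

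Two things follow. A reader who takes the sentence literally has the wrong operating characteristic for the gate. And the gate is stricter than the sponsor's declared tolerance of 0.20 requires, at a decision where a missed effect can stop development before Phase III.

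**Working it through.** **Inputs**
- Three comparisons at 0.067 each (Phase II/1).
- Allocation 3:3:3:1:1:1 with 189 active patients, so 189 / 3 = 63 per active arm, and 63 in the pooled placebo group (Phase II/1; Sample size).
- One pooled control (Statistical methods).
- Assumptions: normal approximation for the slope contrasts, and equal slope variance and information per patient across arms. Sidedness is not stated. The two-sided case comes first because the article speaks of treatments that differ significantly from placebo; the one-sided case follows.

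**1. The article's own figure.** 0.20 / 3 = 0.0667, printed as 0.067, and 3 × 0.0667 = 0.20. The stated value reproduces as the Bonferroni sum. (With the rounded level the sum is 0.201, a rounding difference only.)

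**2. Correlation between comparisons.** Let V be the variance of one arm's mean slope. Each contrast has variance V + V = 2V. Two contrasts share only the placebo term, so their covariance is V and their correlation is V / 2V = 0.5.

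**3. Attained familywise error under the global null.** With critical value c and ρ = 0.5,

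FWER = 1 − ∫ [Φ((c − √ρ·u)/√(1−ρ)) − Φ((−c − √ρ·u)/√(1−ρ))]³ φ(u) du.

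- Two-sided at 0.067: c = 1.832, FWER = 0.164. A simulation of 4 million draws gives 0.1643.
- One-sided at 0.067 (the second Φ term is dropped): c = 1.499, FWER = 0.154.
- For comparison, independent two-sided tests would give 1 − (1 − 0.067)³ = 0.188.
- If the correlation were 0.25 or 0.75, the two-sided value would be 0.182 or 0.136.

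**4. Dunnett level for a global 0.20.** Solving the same expression for FWER = 0.20:
- Two-sided: c = 1.733, which is 0.083 per comparison.
- One-sided: c = 1.339, which is 0.090 per comparison.

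**5. Effect on power per comparison.** If power under Bonferroni is p, the standardised effect is c_B + z_p, and power under Dunnett is Φ(c_B + z_p − c_D). For p = 80%, two-sided: 1.832 + 0.842 − 1.733 = 0.941, and Φ(0.941) = 82.6%. The relative sample size for equal power is ((c_D + z_p)/(c_B + z_p))².

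| Assumed power, Bonferroni | Dunnett, two-sided | Relative n, two-sided | Dunnett, one-sided |
|---|---|---|---|
| 70% | 73.3% | 0.918 | 75.3% |
| 80% | 82.6% | 0.928 | 84.2% |
| 90% | 91.6% | 0.938 | 92.5% |

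The starting powers are illustrative, because the article states none for this stage.

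**The case against.** The strongest reply is that nothing is wrong with the plan. It names Bonferroni and quotes the level that Bonferroni guarantees, as is customary. The bound errs on the safe side, so no false-positive risk is understated. Bonferroni also holds whatever the correlation, whereas a fixed Dunnett level of 0.083 depends on a correlation of 0.5, which missing late swabs or unequal variances could shift. All of this stands. A reader might infer that the stated 0.20 means the error rate is miscalculated or uncontrolled; the article does not support that, since 0.20 is a correct upper bound. The fault in wording is only that a ceiling is given as the attained value.

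Three further inferences are tempting and also unsupported. One is that 0.20 was chosen to avoid discarding a useful drug: the article gives no reason for the figure. Another is that the power gain is free: it needs no extra patients, but all of it comes from letting the actual error rise from about 0.16 to 0.20. The third is that a known amount of power is being lost: without a stated power, only a range can be shown.

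Timing is also a fair objection. Current status reports 256 patients randomized by July 2021, against 252 planned for this stage. Loosening the criterion after efficacy data have been seen would be open to the charge of being driven by the data. Amendments also need ethics approval before they are implemented.

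The objection does not remove the main point. At the global level the plan itself declares, a standard and more powerful method exists for comparisons with a shared control, and the correlation can be estimated from the fitted model instead of being fixed in advance.

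**Conclusion.** The point holds as an efficiency and wording improvement. The Phase II/1 test is valid and conservative: its familywise error is about 0.164 (two-sided) or 0.154 (one-sided) where the article says it will be 0.20. Using the declared 0.20 through Dunnett's test would add about 1.6 to 3.3 percentage points of power per comparison if two-sided, equivalent to about 6% to 8% fewer patients for the same power, and somewhat more if one-sided. These figures rest on planned group sizes of 63, equal slope variances, a normal approximation and assumed starting powers. The gain is modest, and its importance comes from the gate being able to end the trial.

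**What to change.** Preferred, if it can be documented before anyone has seen unblinded efficacy data: replace Bonferroni with Dunnett's many-to-one test at the declared global 0.20. Take the correlation between the three slope contrasts from the fitted mixed model and compute the critical value for the actual group sizes. At the planned sizes this is about 0.083 per comparison if two-sided. State the sidedness.

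If Bonferroni is kept, or efficacy data have already been seen: leave the 0.067 threshold alone and restate the global error as *at most 0.20 (about 0.16 with the shared placebo)*, or about 0.15 if the tests are one-sided.

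Cost: a sentence or two in the article and the analysis plan, with no extra patients or data. The Dunnett option also needs the amendment approval that the article requires, and it accepts an actual familywise error of 0.20 and reliance on the shared-control correlation. The wording option costs nothing beyond the edit.

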#### Interventions

Intervention drugs administered in each stage

**Phase II, first stage -** six arms with six different interventions will be designed:

ATV.DCV.SOF/DCV.PbO ATV.PbO DCV.PbO SOF/DCV.

**Phase II, second stage -** four arms with four different interventions will be designed:

Best of the first stage.Best of the first stage + the second best.PbO best first stage.PbO best first stage + PbO second best.

**Phase III, third stage -** two arms with two different interventions will be designed:

Best antiviral alone or in combination (defined in Stage 1 or 2).PbO best antiviral alone or in combination.

The doses and administration routes of the study drugs are described in table 3. If swallowing is impossible for any reason, the protocol provides for the use of the study drugs via a nasogastric or nasoenteral tube. The study drugs will be donated by pharmaceutical companies, with ATV (and PbO) donated by Fundação Oswaldo Cruz (Fiocruz) and DCV, SOF and respective PbOs donated by Blanver Farmoquímica e Farmacêutica.

**Table 3 t3:** Study drug dosage

Drug	Pharmaceutical form	Route of administration/ instructions for use	Frequency of administration	Conservation
Daclatasvir/placebo DCV	Coated tablets/ 28 tablets bottles*	Orally with or without food	2 tablets once daily on D1, 1 tablet once daily from D2 to D10	Room temperature 15 to 30°C
Sofosbuvir/placebo SOF	Coated tablets/ 28 tablets bottles*	Orally with or without food	1 tablet twice daily on D1, 1 tablet once daily from D2 to d10	Room temperature 15 to 30°C
Atazanavir/placebo ATV	Capsules with packs of 30 capsules*	Orally with food	2 capsules twice daily on D1, 1 capsule twice daily from D2 to d10	Room temperature 15 to 30°C

DCV - daclatasvir; SOF - sofosbuvir; ATV - atazanavir; D - day.

* Coated tablets for daclatasvir and sofosbuvir treatments and placebos and capsules for atazanavir treatment and placebo are identical in physical appearance.

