#### Rules for changing the study stage (Figure 2)

**Figure 2 f2:**
[figure not shown]
Rules for changing stages. SOF - sofosbuvir; ATV - atazanavir; DCV - daclatasvir.

If ATV and a presentation of DCV alone are effective and safe in the first stage, a second stage will be performed with the first- and second-best drugs from the previous stage combined according to the rate of decay of the viral load logarithm (slope). The drug with the highest decay rate will be administered first, followed by the drug with the second highest decay rate. The third phase will investigate the drug with the highest decay rate in Phase II/1 or Phase II/2.If only DCV presentations are effective and safe, a Phase II/2 trial will not be conducted, and Phase III will start with the formulation of DCV alone or combined with SOF which produces the higher rate of decay and it is safe according to the interpretation of the DSMB.If only ATV is effective and safe, a Phase II/2 will not be conducted, and Phase III starts with ATV alone.If none of the study drugs are effective and safe in Phase II/1, the study ends without conducting Phase II/2 and/or Phase III.

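### The stage-change rules and the Phase II/1 analysis section contradict each other on entry to Phase II/2, and pairing by slope rank can combine two daclatasvir-containing arms

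*Protocol article*

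**What the plan says.** The protocol article describes the decision after Phase II/1 in three places.

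- **Rules for changing the study stage (Figure 2).** The second stage depends on joint success: "If ATV and a presentation of DCV alone are effective and safe in the first stage, a second stage will be performed". Its pair is then chosen purely by ranking on slope, fastest decay first. If only DCV presentations succeed, Phase II/2 is skipped and Phase III starts with the better one. The ATV case is parallel: "If only ATV is effective and safe, a Phase II/2 will not be conducted". ATV by itself then goes directly to the third stage. If nothing is effective and safe, the study ends.
- **Analysis of primary outcomes, Phase II/1.** The study ends here only if no arm differs significantly from pooled placebo. Otherwise selection begins "Among the treatments significantly different from the PbO group in relation to the linear rate of viral load decay": the arm with the fastest decay that the safety committee accepts becomes a candidate for Phase II/2. Then: "It will be combined with the drug responsible for the second highest linear decay rate to comprise the second Phase II/2 treatment group". No route straight to Phase III appears, and the section does not refer to the stage-change rules.
- **Interventions.** The first-stage arms are "ATV.DCV.SOF/DCV.PbO ATV.PbO DCV.PbO SOF/DCV", so two of the three active arms contain DCV. The second-stage combination is defined only as "Best of the first stage + the second best".

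Table 1 gives the Phase II/2 objective as comparing combinations of antivirals with single ones on viral-load decay.

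**The concern.** This is the main adaptive decision of the trial. It settles whether Phase II/2 is run at all, which regimens it contains and what is carried into Phase III, whose analysis also reuses patients from both Phase II stages. Two problems arise.

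1. **Entry.** For some Phase II/1 results one section opens Phase II/2 and the other forbids it. If nothing sets an order of precedence, the choice between them could be made after the slopes are known.
2. **Composition.** The trigger in the stage-change rules requires ATV to succeed, but the pair is then picked by slope rank alone. Because DCV appears in two of the three ranked arms, the top two can be DCV and SOF/DCV. ATV, whose success helped to open the stage, would then be absent from it.

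The Current status section reports 256 patients randomised against a Phase II/1 target of 252, so this decision comes next.

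**Working it through.** **The article's own figures.** Per-comparison level: 0.20 / 3 = 0.0667, printed as 0.067. Sizes: 4 × 63 = 252 for Phase II/1 and 3 × 63 = 189 for Phase II/2; 252 + 189 + 564 = 1,005. All reproduce. No printed number is wrong here; the problem lies in the rules.

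**Entry rule.** Three active arms give 2³ − 1 = 7 non-empty sets of effective and safe arms. The Phase II/1 section is read literally, so the partner is the arm with the second highest slope whether or not it is significant.

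| Effective and safe | Stage-change rules | Phase II/1 section | Agree? |
|---|---|---|---|
| ATV | Phase III | Phase II/2 | No |
| DCV | Phase III | Phase II/2 | No |
| SOF/DCV | Phase III | Phase II/2 | No |
| DCV, SOF/DCV | Phase III | Phase II/2 | No |
| ATV, DCV | Phase II/2 | Phase II/2 | Yes |
| ATV, SOF/DCV | Phase II/2* | Phase II/2 | Yes* |
| All three | Phase II/2 | Phase II/2 | Yes, but see composition |

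*If SOF/DCV counts as a presentation of DCV; the wording "If ATV and a presentation of DCV alone are effective and safe in the first stage, a second stage will be performed" leaves this open.

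The rules conflict in 4 of 7 sets. If the second highest slope is instead ranked only among significant arms, the three single-arm sets have no partner. The Phase II/1 section is then silent on them, not contradictory. The set {DCV, SOF/DCV} still conflicts: two significant arms can be ranked and combined under one section, while the other skips the stage.

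**Composition when all three arms succeed.** Phase II/2 has two active regimens: the best, and the best plus the second best.

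- SOF/DCV first, DCV second: the regimens are SOF/DCV and SOF/DCV + DCV. Both contain the same drugs, so there is no combination-versus-single contrast.
- DCV first, SOF/DCV second: the regimens are DCV and DCV + SOF/DCV. In drug content this repeats a contrast already available in Phase II/1.

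ATV is left out in both cases.

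**Size, under assumptions.** The article gives no Phase II/1 effect size or power.

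- *Ranking.* With equal true slopes and equal arms of 63, each arm is equally likely to rank last. P(ATV last) = 1/3, so the DCV-containing arms are the top two in one third of trials. This is not conditioned on all three passing.
- *Conflict, equal effects, 50% power per comparison.* Equal arms sharing one placebo group of the same size give a correlation of 0.5 between comparisons. Ignoring significance in the wrong direction, P(one given arm significant) = 1/2, P(two given arms) = 1/4 + arcsin(0.5)/(2π) = 1/3, and P(all three) = 1/8 + 3·arcsin(0.5)/(4π) = 1/4.
  - P(at least one) = 3/2 − 3 × 1/3 + 1/4 = 3/4.
  - P(ATV and at least one DCV-containing arm) = 1/3 + 1/3 − 1/4 = 5/12.
  - Literal conflict = 3/4 − 5/12 = 1/3, that is (1/3)/(3/4) = 44% of results with at least one significant arm.
  - Narrower reading, only {DCV, SOF/DCV}: 1/3 − 1/4 = 1/12, that is (1/12)/(3/4) = 11%.
- *Higher power, by simulation (two-sided 0.067, safety assumed met).* With equal effects the literal conflict share is 20% at 80% power and 10% at 90%. If only ATV works it is 90 to 93%, and if only the DCV family works 95 to 97%, at 50 to 90% power.
- *All three pass and both DCV-containing arms lead, equal effects.* 8%, 20% and 26% of trials at 50%, 80% and 90% power.

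**The case against.** The strongest defence is that the stage-change rules govern. They are headed as such, give an explicit action for only-ATV, only-DCV and no-success results, and treat DCV and SOF/DCV as presentations of one drug. The Phase II/1 section is about analysis. It calls the best arm a candidate, which can be read as subject to those rules, and its ranking may be meant only within the significant set. On the same contextual reading, the two best drugs would be ATV and a DCV presentation. Figure 2, the SAP and the DSMB charter are not shown and may settle precedence.

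Part of this stands. Read alone, the stage-change rules give a clear action for only-ATV and only-DCV results, and the narrower ranking removes the single-arm contradictions. It does not remove the {DCV, SOF/DCV} conflict, because the sentence on combining is unconditional and carries no cross-reference. Nor does it cure the all-three case, where every section defines the pair by rank.

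A reader might infer three stronger points that the article does not support.

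- **That an arm clearing virus significantly more slowly would keep the trial open**, since the Phase II/1 test names no direction. The Introduction, Table 1 and the stage-change rules all require a reduction in viral load or effectiveness, so direction is fixed; the wording is merely loose.
- **That the decision is undefined in likely outcomes.** Contradictory is the accurate word, and likelihood cannot be shown without an effect size. At an assumed 99% power, with ATV and SOF/DCV effective and DCV null, either problem arises in only 1.7% of results with a significant arm.
- **That the DCV pairing would usually occur.** Shares of 63% and 87% follow if the DCV presentations truly exceed ATV by 1 or 2 standard errors of an arm slope. Those advantages are assumed, and the shares are not conditioned on all three arms passing.

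**Conclusion.** The point holds as a contradiction between sections plus a defect in how the pair is formed. On the literal text the entry rules disagree in 4 of 7 outcome sets; on the reading most favourable to the Phase II/1 ranking they still disagree in one. The disagreement decides whether the 189-patient Phase II/2 is run. In the all-three outcome, ranking by slope can leave Phase II/2 with no combination-versus-single contrast, or with one that only repeats Phase II/1.

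The counts of outcome sets and the 189 come from the text alone. Every probability rests on assumed effects, and those for conflict also on assumed power; the one third requires equal true slopes. Whether an unseen document sets precedence is unknown, but that would not make the published sections consistent.

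**What to change.** Before any Phase II/1 slopes are seen, reconcile the Interventions section, the stage-change rules with Figure 2, the Phase II/1 analysis section, the SAP and the DSMB charter into one entry rule. It should state:

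1. the action for each of the seven sets of effective and safe arms, and for none, including whether SOF/DCV meets the DCV part of the trigger;
2. whether the partner must itself be effective and safe, and among which arms it is ranked;
3. how the combination is formed when both DCV-containing arms rank highest, so that Phase II/2 still tests a combination against a single antiviral.

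Which entry rule and which combination apply is for the sponsor to decide; this review takes no position. If slopes have already been seen, record which rule was applied and when it was fixed.

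As a minor alignment, replace the direction-free test wording in "Among the treatments significantly different from the PbO group in relation to the linear rate of viral load decay" with wording that matches effectiveness as used in the stage-change rules.

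The cost is document wording only. No additional patients or data are needed.
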